## Abstract

**Background:**

Prostate cancer survivors (PCS) experience long-term side effects beyond treatment such as fatigue, depression and anxiety. Quality and engaging supportive care programs are needed to reduce these chronic and debilitating effects. Independent of physical activity (PA), high volumes of sedentary behavior (SB) are associated with chronic disease-related risk factors and poorer cancer-specific quality of life (QoL). Simultaneously increasing PA and decreasing SB may be an effective health promotion strategy. Given that PCS may face several barriers to engaging in supervised programs, there is a need to develop and assess the efficacy of interventions that employ distance-based approaches for behavior change. The primary aim of this study is to determine the effects of a 12-week intervention (Fitbit + behavioral counselling) vs. Fitbit-only control group in reducing SB among PCS. Secondary outcomes include light-intensity PA, QoL, motivational outcomes, and patient satisfaction.

**Methods:**

This two-armed, randomized controlled trial will recruit inactive PCS (stage I-IV) across Canada who self-report engaging in >8 hours/day of SB. Participants will be randomized to the intervention (*n*=60; Fitbit and behavioral support) or active control group (*n*=60; Fitbit-only). The intervention consists of the use of a Fitbit and a series of six behavioral support sessions (two group, four individual) to aid PCS in gradually replacing SB with light-intensity PA by increasing their daily step counts to 3,000 steps above their baseline values. The Fitbit-only control condition will receive a Fitbit and public health PA resources. The primary outcome is change in SB measured objectively using activPAL inclinometers. All secondary outcomes will be measured via self-report, except for PA which will be measuring using Fitbits. Data will be collected at baseline, post-intervention, and at 6-month post-intervention.

**Discussion:**

Reducing SB and increasing light-intensity PA plays an important, yet often undervalued role in the health and well-being of PCS. This study will create a unique distance-based platform that can be used by clinical and community-based organizations as a low-cost, supportive care tool to improve health outcomes for PCS.

**Trial Registration:**

ClinicalTrials.gov Identifier NCT05214937. Registered January 28, 2022

Protocol version: v.1

## Background

The ten-year relative survival rate for prostate cancer for all stages combined is 90%, resulting in a growing number of prostate cancer survivors (PCS) [1]. Many PCS suffer from long-term side effects well beyond treatment, such as urinary incontinence, erectile dysfunction, fatigue, depression, and anxiety [2–4]. Supportive care interventions are needed to reduce the chronic effects of cancer and its treatment during the transition into survivorship. Physical activity (PA) has a positive impact on many clinical outcomes, including improved quality of life (QoL), cancer-specific mortality, and reducing treatment-related toxicities among PCS [5–8]. Despite this, few PCS achieve current PA guidelines [9–11], and there is a significant decrease in PA during and after adjuvant therapy [12]. Short-term supervised PA programs have been successful in improving fitness and patient-reported outcomes in PCS [13], but uptake and adherence remain low [14].

Independent of PA, addressing prolonged periods of sedentary behavior (SB) has numerous beneficial health outcomes, including a reduced risk of mortality [15–19] and improved QoL [20–22]. SB is defined as any waking behavior characterized by a low energy expenditure (i.e., ≤1.5 resting metabolic equivalents) while in a sitting, reclining, or lying down posture [23]. In Canada, 5.8% of all associated cancers is attributable to SB, with increased cancer risk for ≥6 hours per day of SB [24]. PCS spend most of their day sedentary (i.e., 69% of waking hours) or engaged in light-intensity PA (LPA; 30% of waking hours) compared to moderate-to-vigorous intensity PA (MVPA; 1% of waking hours) [11], thus providing more opportunities to address SB in a day. As such, focusing on reducing SB among PCS may be a more feasible intervention approach than supervised exercise. A pooled analysis examining associations between PA, SB, and percentiles of QoL showed that ≥30-minute bouts of SB are inversely associated with functional well-being [20]. Similarly, LPA appeared to be beneficial for QoL even amongst those with the poorest QoL distributions [20]. Simultaneously increasing MVPA and reducing SB produced clinically relevant changes in QoL (i.e., physical and role function) for PCS [20, 25]. Despite the growing evidence that reduced SB may result in better QoL, there are no known effective strategies aimed at reducing SB among PCS. However, given the independent effects of increasing PA and minimizing time spent in SB on health outcomes, interventions should not only target reductions in sedentary time, but also replacing that behavior with light-intensity PA.

Developing theory-driven interventions is critical for facilitating adoption and maintenance of behavior change [26]. For successful behaviour change, it is necessary to move beyond intention-focused theories towards psychosocial and behavioural constructs proposed to reduce the intention-behaviour gap, which may be more effective for behavior change [26]. One such approach is the Multi-Process Action Control (M-PAC) framework, which builds on the well-established social cognitive antecedents of PA behavior, while also recognizing the intention-behavior gap [26]. The M-PAC framework has a layered, progressive structure where an individual moves from intention formation to adoption of action control and onto maintenance of action control. Intention formation is predicated on initiating reflective processes (i.e., instrumental attitude and perceived capability). Reflective processes are hypothesized to influence intention formation and initiate regulatory processes to enact this intention (i.e., affective attitude and perceived opportunity). The translation of intention into PA (i.e., action control) is determined partially by regulatory processes (e.g., action planning, coping planning, self-monitoring, social support) during the initial adoption of the behavior. Continuation of PA action control is thought to include the addition of reflexive processes (e.g., habit) for maintenance of behavior change. The utility of the M-PAC framework for successful behavior change has shown promise in an exercise telephone counselling intervention in hematological cancer survivors [27], however, no study to date has examined a theory-based intervention in SB in PCS or any other cancer survivor group.

Though supervised interventions have been effective in increasing PA behaviors among cancer survivors [13], distance-based interventions are an attractive alternative due to the ability to reach a large number of cancer survivors, accessibility, and lower cost. Wearable technology activity monitors (e.g., Fitbit) are a relatively low-cost, self-management tool that have a wide reach and broad applications for use in clinical and public health settings. Initial interventions using wearable technology activity monitors have shown promising improvements in PA and SB [28, 29]. A previous pilot study conducted by our research group examined the feasibility of a *m*health application (RiseTx) for reducing SB and increasing MVPA among PCS undergoing androgen deprivation therapy (ADT) [30]. PCS were given an activity tracker, access to the RiseTx *m*health web application, and a goal of increasing step counts by 3,000 daily steps above baseline levels over 12-weeks. A range of behavior change support tools were progressively deployed to reduce SB (e.g., self-monitoring of steps; action planning). The RiseTx *m*health application was successful in reducing device-measured SB by 455 minutes/week and increasing MVPA by 44 minutes/week, as well as increasing daily steps by 1535 between baseline and post-intervention [30]. The current study will build on this successful pilot study and harness the many lessons learned during the implementation of RiseTx. As an extension of this prior work, the current intervention will provide additional synchronous behavioral support aligned with processes in the M-PAC framework through videoconferencing to reduce SB. We are replacing the web-platform with 1:1 videoconferencing with a movement specialist in response to feedback from the original RiseTx participants.

The primary objective is to determine the effects of the 12-week intervention (i.e., Fitbit + behavioral counselling) compared to a control condition (Fitbit + public resources) in reducing SB in PCS. It is hypothesized that the intervention group will decrease their SB compared to the Fitbit-only control condition at post-intervention (12 weeks) and 6-month follow-up. Secondary objectives are to determine the effects of the intervention on secondary outcomes including changes in MVPA, LPA, motivational outcomes from the M-PAC framework, physical function and patient-reported outcomes (i.e., QoL, fatigue, disability and mental health) compared to the Fitbit-only control group.

## Methods/Design

This study protocol follows the SPIRIT guidelines [31]. Ethics approval was granted by the Research Ethics Board at the University of Toronto (protocol #41699). The trial was registered with the ClinicalTrials.gov database on January 28, 2022 (NCT05214937).

### Study Design

The intervention is a two-armed, parallel groups randomized controlled trial. Following baseline assessments (T_1_), participants will be randomized to one of two groups: 1) an intervention group in which they receive a FitBit, SB workbook, and behavioral counselling or 2) a control group in which they receive a Fitbit and publicly available health education resources (Fitbit-only control). Follow up assessments will take place immediately after the 12-week intervention period (i.e., post-intervention; F_1_) and 9 months from baseline assessments (i.e., 6-month post-intervention; F_2_). The participant flow through the study is summarized in Fig. 1.

**Fig. 1 Fig1:**
[figure not shown]
Participant flow through the study

### Recruitment and Procedures

#### Participant Eligibility

PCS are eligible to participate if they are: 1) ≥18 years of age; 2) have been diagnosed with localized or asymptomatic metastatic primary prostate cancer; 3) are not currently undergoing radiation or chemotherapy; 4) self-report >8 hours of SB/day during waking hours; 5) are inactive (self-report <150 minutes of MVPA per week); 6) in the contemplation or preparation stage for motivational readiness to change as determined by the Stages of Change Questionnaire [32]; 7) have access to a smartphone, tablet, or computer with a webcam and reliable internet access; 8) received physician clearance to participate if indicated by the Physical Activity Readiness Questionnaire (PAR-Q+); 9) currently reside in Canada and plan to stay in Canada for the next 12 months; and 10) are proficient in English. PCS will be ineligible if they: 1) have a medical condition that prohibits walking (e.g., severe hip or knee arthritis); 2) have been diagnosed with another primary or recurrent invasive cancer (i.e., other than non-melanoma skin cancer); and 3) use a gait aid device.

#### Participant Recruitment

Participants will be recruited from Toronto and Vancouver sites through community partnerships and connections with the genitourinary clinics at the Princess Margaret Cancer Centre in Toronto and the Survivorship and Primary Care Program at BC Cancer. Clinicians will be informed of the study through presentations by the investigative team at rounds, and potential participants will be introduced to the study by their oncologist or clinic nurse. Participants will also be recruited through advertisements in local community cancer organizations, on social media, as well as recruitment e-mails sent out through relevant listservs.

#### Screening Procedure and Informed Consent

Study personnel will complete initial screening of the PCS by phone to ensure they meet the eligibility criteria. Certified exercise physiologists (e.g., American College of Sports Medicine [ACSM], Canadian Society of Exercise Physiologists [CSEP]) who are also part of the study team will provide clearance for eligible participants or obtain physician clearance if required. Written consent will be obtained by all participants in the study.

#### Randomization

Randomization will be performed by study personnel using a stratified randomization scheme via REDCap. The sequence will be random, permutated blocks of varying sizes, stratified by ADT use (i.e., ADT vs. no ADT). PCS will be assigned in a 1:1 ratio to either the intervention or control group. Randomization codes will be kept in a digital file that is separate from other study records. Only the study co-ordinators and investigators will have access to the randomization codes.

#### Blinding

Study personnel and participants will be blind to group allocation during baseline as randomization will take place after completion of all baseline measures. Subsequent data collection appointments will be completed by study personnel that are blind to the group allocation. Due to the nature of the study, it is not possible to blind the participants to their group allocation.

#### Sample Size

A sample size calculation was performed in G*power based on a multivariate analysis of variance with two intervention levels (i.e., intervention, control) and two dependent variables (i.e., SB and PA). Based on our pilot trial with PCS, we assumed a medium effect size of Cohen’s *d* = 0.50 at the end of the intervention. Based on an alpha of 0.05 and power of 0.80, a total sample size of 100 is required. To account for the expected 20% attrition, a sample of 120 PCS (intervention *n* = 60, control *n* = 60) will be recruited.

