##### Statistical Analyses

Linear mixed models will be used to model the primary outcome (i.e., SB) and secondary outcomes (i.e., LPA, motivational outcomes from M-PAC, QoL) at the three time points. Fixed effects included in the models will be time (i.e., baseline, 3-month, 6-month post-intervention), group (i.e., intervention, control), and the interaction. A random intercept will be included to account for variance between and within participants. All models will be estimated while adjusting for covariates (e.g., baseline SB, age, treatment type). Sensitivity analyses will be performed to test for informative dropouts.

The same analytic approach will assess subgroup differences of participants which will include several standard demographic (e.g., age, gender), fitness (e.g., baseline PA) and clinical variables (e.g., time since treatment, disease stage) by modeling the changes over time from post-intervention (F_1_: 3-months after baselines) to 6-month follow-up (F_2_: 9-months after baseline). An intention to treat analysis will be conducted based on all available data from PCS randomized regardless of non-adherence during the intervention. Participants with missing data will be included under the missing-at-random assumption of the mixed-model analysis.

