Given that cancer survivors may face several barriers to engaging in PA programs, there is a need to develop and assess the efficacy of interventions that employ distance-based approaches (e.g., characterized by limited face-to-face contact and/or supervision) [73]. Groen et al. [73] conducted a systematic review examining distance-based PA behavior change interventions for cancer survivors where the results show that intervention effects on PA were small and new approaches were needed. The current study will build on our successful pilot study by using a more robust clinical design and focusing on maintenance of behavior change in two important ways. A series of behavioral counselling sessions based on the M-PAC will be adapted throughout the trial that move beyond intention formation to focus on maintenance. This is noteworthy as theory-based interventions result in meaningful changes in behavior compared to atheoretical approaches in cancer survivors [74], including PCS [75]. Finally, our prior work was a single-group feasibility study, while this current study will examine the effects of the intervention on SB in a well-powered RCT. Overall, the current intervention will move from a feasibility to an efficacy trial, focus on maintenance grounded in theory (e.g., M-PAC), include sustainable wearables (e.g., Fitbit) that could be integrated within typical delivery models of cancer care.

Cancer survivorship is now recognized as an essential cancer care component, and greater efforts on maintaining QoL is needed. Cancer Care Ontario published specific follow-up care guidelines for PCS [76]. These guidelines aim to promote comprehensive follow-up care, optimal health, and QoL in PCS, which includes health promotion (i.e., PA) and management of physical and psychosocial side effects. Therefore, decreasing SED and increasing PA may be an effective health promotion strategy for PCS. The current intervention has high potential for broad reach and impact on both PCS and their support networks, as it can ultimately be delivered safely through internet- and mobile-based applications. With internet usage growing fastest among older Canadians [77], our study will create a unique distance-based platform that could be scaled for use by clinical and community-based organizations as a low-cost, supportive care tool to improve QoL for all cancer survivors across Canada.

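### The sample size is computed for a two-outcome MANOVA on SB and PA that the trial does not run, so 80% power is not established for the primary outcome, activPAL SB

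*Protocol article*

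**What the plan says.** - **Sizing (Sample Size).** The calculation is for a "multivariate analysis of variance with two intervention levels (i.e., intervention, control) and two dependent variables (i.e., SB and PA"). On the effect: "we assumed a medium effect size of Cohen’s *d* = 0.50 at the end of the intervention", credited to the group's pilot. Then: "Based on an alpha of 0.05 and power of 0.80, a total sample size of 100 is required". Then: "To account for the expected 20% attrition, a sample of 120 PCS", 60 per arm.
- **Primary outcome (Abstract, Methods).** "The primary outcome is change in SB measured objectively using activPAL inclinometers". The primary objective at the end of the Background concerns SB only. Table 2 lists activPAL SB as the only primary outcome and puts objectively measured PA under secondary outcomes.
- **Analysis (Statistical Analyses).** "Linear mixed models will be used to model the primary outcome (i.e., SB") and the secondary outcomes, with time, group and their interaction as fixed effects and a random intercept. Baseline SB is among the covariates. No MANOVA and no joint test of SB and PA appears.
- **Claim (Discussion).** The trial will "examine the effects of the intervention on SB in a well-powered RCT". The same paragraph describes the prior work as a single-group feasibility study.

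**The concern.** The sizing test and the deciding test address different hypotheses. A two-outcome MANOVA rejects when SB and PA taken jointly differ between arms, and PA alone can drive that rejection. Its power is not the power to show an effect on SB. The article states both the sizing method and the analysis method, so this is not a detail left to a fuller document.

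The effect size has a related weakness. A single-group pilot yields a before-after change. It cannot estimate a difference against a control arm that also receives a Fitbit.

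What is at stake is how the result is read, above all a null result on SB. Readers would set it against an 80% figure that was not computed for SB.

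**Working it through.** **Inputs from the protocol.** d = 0.50, alpha 0.05, power 0.80, N = 100, 120 recruited and 20% attrition (Sample Size); 1:1 allocation (Randomization). Expected completers: 120 × 0.80 = 96, or 48 per arm.

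**Not given, so assumed or varied.** The correlation between SB and PA; the correlation r between baseline and follow-up SB; the SD unit in which d is expressed; the sidedness, taken as two-sided because a MANOVA F test is non-directional.

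**1. Reproducing N = 100 as a MANOVA**

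- *Global two-group test on two outcomes (Hotelling T²).* F has (2, N − 3) degrees of freedom and noncentrality N·f². With f² = 0.10, N = 100 gives power 0.803. If d = 0.50 on both outcomes (signs aligned) with correlation c, then D² = 2(0.50²)/(1 + c) and f² = D²/4. Setting c = 0.25 gives D² = 0.40 and f² = 0.10.
- *The same test at other correlations.* c = 0, 0.5 and 0.7 give N = 81, 119 and 135.
- *Repeated-measures MANOVA, between-factors routine.* Two groups, two measures, f = d/2 = 0.25 and noncentrality N·f²·2/(1 + c). At c = 0.5, N = 98 reaches 80%.

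So 100 is reachable, with a correlation of about 0.25 to 0.5 depending on the routine.

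**2. SB alone, no credit for baseline adjustment**

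Two-sample t test with n per arm, noncentrality d·√(n/2) and 2n − 2 degrees of freedom.

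| Analysed | n per arm | Noncentrality | Power |
|---|---|---|---|
| 96 | 48 | 2.449 | 67.9% |
| 100 | 50 | 2.500 | 69.7% |
| 120 (no loss) | 60 | 2.739 | 77.5% |
| 128 | 64 | 2.828 | 80.1% |

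The d detectable with 80% power is 0.57 with 100 analysed and 0.58 with 96.

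**3. SB alone, 96 analysed, using the baseline measurement**

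With d in follow-up SD units and equal SDs at both times, the effective d is d/√(1 − r²) for a baseline-adjusted comparison and d/√(2(1 − r)) for an unadjusted change score. At r = 0.5 these are 0.50/√0.75 = 0.577 and 0.50/√1 = 0.50.

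| Assumed r | Baseline-adjusted | Change score |
|---|---|---|
| 0.3 | 72% | 54% |
| 0.4 | 75% | 60% |
| 0.5 | 80% | 68% |
| 0.6 | 86% | 77% |
| 0.7 | 92% | 88% |

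**4. The scale of d matters**

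If d = 0.50 is instead in SDs of change, the change-score contrast has 67.9% power at 96 whatever r is. The effective d for the adjusted comparison is then 0.50·√(2(1 − r))/√(1 − r²) = 0.50·√(2/(1 + r)). That is 0.620 at r = 0.3 (85%) and 0.598 at r = 0.4 (83%). The protocol does not say which scale applies.

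**The case against.** **The trial has about 70% power, not 80%.** A reader might infer this from the 69.7%. The protocol does not support it. That figure belongs to an unadjusted t test, which the trial does not run either. The analysis section lists baseline SB as a covariate, and under adjustment 80% is reached with 96 analysed at r of about 0.5 and exceeded above that. The objection stands: power for the planned test is undetermined, not shown to be 70%.

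**The 100 is a miscalculation.** A reader might also infer this, because d = 0.50 on one outcome needs 128. It does not follow. The section claims a MANOVA, and two MANOVA routines give 98 to 100. What is wrong is the choice of test, together with an undisclosed correlation.

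**A one-sided test would rescue the figure.** At one-sided 0.05, 50 per arm gives 79.9%. No one-sided test is stated, so this does not help.

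**The effect is already labelled as assumed.** This is true, and the Discussion is open about the pilot's single-group design. What remains open to objection is crediting a between-arm d to that pilot.

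**Nothing in the data changes.** The recruitment target and the treatment-effect interval stay as they are. That limits the consequence to what is claimed for the design and how a null result is read.

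**Conclusion.** The point holds as a mismatch between the sizing test and the primary analysis. The 80% belongs to a joint SB/PA test that is not planned, so neither it nor the Discussion's power claim is established for activPAL SB.

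Without credit for baseline adjustment, the recruited 120 fall short of 80% at d = 0.50 even with no dropout (77.5%); with the planned attrition, power is 67.9%. With adjustment, and d in follow-up SD units, the range at 96 analysed is 72% to 92% for r from 0.3 to 0.7. All of this rests on d = 0.50, a two-sided 0.05 level and, for the adjusted figures, a correlation that the protocol does not supply. The trial may have adequate power; the protocol does not show that it does.

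**What to change.** Keep 120 participants. In Sample Size, replace the MANOVA statement with power for the between-arm SB contrast at F1, with 96 analysed and two-sided alpha 0.05.

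- Take the contrast from the primary model exactly as it will be fitted. The analysis section lists baseline both as a level of time and, for SB, as a covariate. It should be clear whether the contrast is a baseline-adjusted difference or a difference in change, since step 3 shows that the two have different power.
- State the SD and the scale on which d = 0.50 is standardised, and call it an assumption rather than a pilot estimate.
- Give power across a range of baseline correlations.
- In the Discussion, make the well-powered claim conditional on the assumed correlation, or delete it.

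Cost: one rewritten paragraph, the matching Discussion wording, and a conditional, less favourable power figure. If settling the contrast shows that the analysis text is ambiguous, a clarifying sentence is needed there too. No extra patients.

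### Sample size: 120 recruited with 20% attrition leaves 96, four short of the 100 stated as required (a minor arithmetic error)

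*Protocol article*

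**What the plan says.** All the figures stand in the Sample Size section of the protocol article.

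- The calculation was done in G*Power, "based on a multivariate analysis of variance with two intervention levels" and two dependent variables, sedentary behavior (SB) and physical activity.
- On the effect size: "we assumed a medium effect size of Cohen’s *d* = 0.50 at the end of the intervention".
- The result: "Based on an alpha of 0.05 and power of 0.80", "a total sample size of 100 is required".
- The allowance for dropout: "To account for the expected 20% attrition, a sample of 120 PCS", given as 60 per arm.

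The Randomization section adds that "PCS will be assigned in a 1:1 ratio to either the intervention or control group". No other section gives a different attrition rate, a different target, or a rule for replacing participants who drop out. The Statistical Analyses section plans linear mixed models on all available data from randomized participants, under a missing-at-random assumption.

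**The concern.** The section names a number needed, a loss expected and a number to recruit, and the third does not follow from the first two. The expected loss is a fraction of the people recruited, so the target has to be divided by the fraction retained. The plan's 120 instead adds 20% of the target to the target.

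At stake is whether the power statement is true at the attrition rate the plan itself expects. This calculation is the only support the article gives for calling the trial well powered in its Discussion, and any reader can check it in one line.

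**Working it through.** **Inputs, all from the Sample Size section unless noted:** required total N = 100; expected attrition d = 0.20; recruited total 120 (60 per arm); alpha 0.05; power 0.80; two groups and two outcomes; 1:1 allocation (Randomization section).

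**1. Reproduce the plan's figure.** N × (1 + d) = 100 × 1.20 = 120. This matches exactly, so rounding is not the explanation.

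**2. Inflate by the retention rate.** N / (1 − d) = 100 / 0.80 = 125. For equal arms this becomes 126 (63 per arm), and 126 × 0.80 = 100.8.

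**3. What 120 delivers at the stated attrition.** 120 × 0.80 = 96; per arm, 60 × 0.80 = 48. The shortfall is 100 − 96 = 4.

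**4. The attrition that 120 does cover.** 1 − 100/120 = 0.167, or 16.7%.

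**5. Effect on power.** The article does not give the MANOVA effect size entered in G*Power, so one has to be assumed. For a two-group MANOVA with two outcomes, power comes from the noncentral F distribution with 2 and N − 3 degrees of freedom and noncentrality f² × N. The value f² = 0.10 is chosen only because it returns a total of 100 at 80% power.

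- N = 100: noncentrality 0.10 × 100 = 10.0, power 80.3%.
- N = 96: noncentrality 0.10 × 96 = 9.6, power 78.5%.
- Loss: 1.8 points.

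Two other settings that need close to 100 participants show the range:

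| Assumed setting | Total N for 80% power | Power at 100 | Power at 96 | Loss |
|---|---|---|---|---|
| MANOVA, f² = 0.10 | 100 | 80.3% | 78.5% | 1.8 points |
| MANOVA, both outcomes at d = 0.50, correlation 0.3 | 104 | 78.6% | 76.8% | 1.8 points |
| One-sided two-sample t-test, d = 0.50 | 102 | 79.9% | 78.4% | 1.5 points |

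The protocol states none of these settings. They are used only to size the drop from 100 to 96, which is about 1.5 to 2 points in each.

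**The case against.** Three arguments can be made for the plan as it stands.

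*The time point of the attrition is not stated.* The effect size is set at the end of the 12-week intervention, while follow-up runs to 9 months from baseline. If the 20% is cumulative to the last visit, attrition at 12 weeks could be 16.7% or less, and 100 or more would remain for the comparison that was sized. This stands as a limit on what can be said about power at 12 weeks. It does not repair the sentence, which applies the 20% directly to the 100 required.

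*The mixed model uses partial data.* Participants lost after the 12-week visit still contribute to the 12-week contrast, and adjustment for baseline SB may recover some precision. This softens the loss. However, the sizing claims no credit for either feature, and a participant with no value after baseline adds little to the group contrast.

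*The shortfall is trivial.* It is small, and that governs how much weight the point deserves. It does not make the figures agree.

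A reader might go further and infer that the trial is materially underpowered, or that it must recruit more people. The documents do not support that. The loss is under 2 points in the settings above, and the exact power cannot be computed because the MANOVA effect size is not given. A reader might also bring in the power of a test of SB alone at d = 0.50. That asks whether 100 was the right base figure, which is a separate question from the attrition step, so it is left out here.

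**Conclusion.** The statement is wrong as written, and the error is minor. On the plan's own three figures, 120 recruited leaves 96, not 100; the inflation should have given 125, or 126 for equal arms. This part needs no assumption beyond applying the stated 20% to the sized comparison, which is the natural reading of the sentence.

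The consequence for power is about 1.5 to 2 points, which puts it slightly below the stated 80%. That size rests on inferred inputs. It also takes 96 evaluable participants at the sized time point, with no gain from partial data or covariate adjustment. Nothing in the planned analysis or the outcomes has to change.

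**What to change.** Keep 120 and replace the attrition sentence in the Sample Size section with wording such as:

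> *A sample of 120 (60 per arm) retains the required 100 if attrition is at most 16.7%; at the expected 20% attrition, 96 (48 per arm) would remain and power would be slightly below 80%.*

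Two details are for the sponsor to supply: the exact power at a total of 96, recomputed from its own G*Power inputs, and the time point to which the 20% refers (12 weeks or 9 months).

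The cost is one sentence and one rerun of the existing calculation, and the stated power becomes slightly less favourable. No extra participants are needed. If the sponsor prefers to hold 100 at 20% attrition, the alternative is to recruit 126, which is six more (126 − 120).
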